**Method/design:**

With the aim of investigating the efficacy and cost-effectiveness of a SSGT, KONTAKT©, a two-armed randomized control trial with adolescents aged 12–17 years (*N* = 90) with ASD and an intelligence quotient (IQ) of over 70 will be undertaken. Following stratification for centre and gender, participants will be randomly assigned to either KONTAKT© or to an active control group, a group-based cooking programme. Participants will attend both programmes in groups of 6–8 adolescents, over 16 one-and-a-half-hour sessions. The primary outcome examined is adolescent self-rated achievement of personally meaningful social goals as assessed via the Goal Attainment Scaling during an interview with a blinded clinician. Secondary outcomes include adolescent self-reported interpersonal efficacy, quality of life, social anxiety, loneliness, face emotion recognition performance and associated gaze behaviour, and parent proxy reports of autistic traits, quality of life, social functioning, and emotion recognition and expression. Cost-effectiveness will be investigated in relation to direct and indirect societal and healthcare costs.

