### Setting

Participants expressing an interest in the study will be invited to a screening session and following determination of their eligibility will take part in a baseline assessment in a university laboratory at Curtin University, Perth, Western Australia. Both the KONTAKT© group and the active control cooking-group will be delivered by AAWA in one of their four metropolitan centres in Perth, Western Australia. The AAWA is the leading service provider for people with ASD in Western Australia, and the only specialist organisation providing a full range of services for children and adults in Australia, with over 700 multi-disciplinary staff.

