Activity 3	Cooking or baking	Every session
Eating the prepared meal	Rating the prepared meal	
Clean up	Washing up, drying dishes, wiping down benches and tables, and sweeping the floor.	Every session
Transition	Recapping the session and feedback to the parents	

The Australian adaptation of KONTAKT©, employing a 16-session variant, aims to improve participants’ communication and social interaction skills, ASD-related traits, and the ability to empathise and adapt in a group setting of 6–8 adolescents aged 12–17 years [19, 21]. Groups meet weekly for an hour and a half, with two trainers delivering a programme underpinned by the principles of cognitive behaviour therapy, behaviour activation, observational learning, psychoeducation, and social cognition training [41, 42]. Sessions scaffold knowledge of common social rules and norms, aiming to promote problem-solving strategies, emotion recognition, and emotion expression [19].

KONTAKT© requires that at least one group trainer is a clinician with extensive experience working with children/adolescents with ASD, who has also received methodological training, or certification in KONTAKT© prior to the programme. Prior to the pilot, Australian clinicians from AAWA were trained by a Swedish team of certified KONTAKT© trainers. Requirements of KONTAKT© training certification include passing this method training, leading at least one KONTAKT© group under supervision, and achieving intervention fidelity as assessed by a KONTAKT© supervisor on the basis of submission of a filmed KONTAKT© session. A KONTAKT©-certified trainer can, in turn, instruct others in delivering KONTAKT©. In the present study, fidelity to the KONTAKT© intervention will be systematically assessed by trainers completing a session by session fidelity checklist, enabling an assessment of intervention fidelity. In addition, attendance sheets will be kept to record the participants’ compliance with the programme, with 80% attendance considered as compliant.

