Super Chef is a manualised cooking-group programme specifically designed for this study (Table 2), with the goal of enabling comparison of KONTAKT© with an active social control group, enabling independent evaluation of the contribution of KONTAKT© to intervention outcomes. As in KONTAKT©, participants allocated to the Super Chef programme will meet weekly in groups of 6–8 for an hour and a half in a 16-session programme moderated by two trainers, one of which will be an occupational therapist with previous experience of working with Australian adolescents with ASD. As with KONTAKT©, each Super Chef session adheres to a specified agenda including discussions, taste testing, individual and group activities, snack time, cooking recipes, eating and rating recipes and cleaning up as rostered. Super Chef was developed by a team including occupational therapists with both clinical and research experience in working with adolescents with ASD, with consideration of the common sensory issues associated with ASD. Fidelity to the Super Chef intervention will be assessed via a fidelity checklist, specially designed for this programme, enabling assessment of the extent to which trainers followed the format of each session.

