### Statistical analyses

As suggested by previous research, reliability of the GAS goals will be investigated via examination of their measurability, equidistance, and difficulty [57]. A random effects regression model will be used to explore those factors associated with the raw data on the GAS scores (dependent variable), over the 9-month duration of the study. Independent variables for the model will be time, group (KONTAKT© versus Super Che’), age, IQ, gender, centre, and comorbidity as fixed effects, with follow up being the primary endpoint of the study. The random effect will be the participant’s ID number, thus accounting for the correlation between measurements made on the same individual within the model.

Analysis of secondary outcomes (interpersonal efficacy, quality of life, social anxiety, loneliness, facial emotion recognition, and eye-tracking behaviour) will be conducted in a similar manner (random effects regression model). Analysis will be based on an intent-to-treat approach [84], considering each participant as belonging to the study group they were initially allocated, regardless of treatment actually received. Missing data will be accounted for according to the guidelines specified for each measure; if no guidance is provided, missing data will be handled in accordance with the CONSORT statement for conducting high-quality RCTs [48]. Data analysis will be conducted using the SPSS version 24 statistical software [88].

The outcomes of the present study will be compared to results obtained by previous evaluations of the short and long variant of KONTAKT© undertaken in Sweden.

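### Both programmes run in training groups of 6–8, but the model's only random effect is the participant; if outcomes correlate within groups, type I error exceeds 5%

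*Protocol article*

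**What the plan says.** **Delivery.** The abstract states: "Participants will attend both programmes in groups of 6–8 adolescents, over 16 one-and-a-half-hour sessions". The interventions section gives each group its own pair of leaders in both arms. For KONTAKT: "Groups meet weekly for an hour and a half, with two trainers delivering a programme". Super Chef participants "will meet weekly in groups of 6–8 for an hour and a half in a 16-session programme moderated by two trainers". According to the Setting section, delivery takes place "in one of their four metropolitan centres in Perth".

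**Analysis.** The Statistical analyses section uses a random effects regression for Goal Attainment Scaling, with follow-up as the primary endpoint. Besides time and arm it enters "age, IQ, gender, centre, and comorbidity as fixed effects". It then adds: "The random effect will be the participant’s ID number, thus accounting for the correlation between measurements made on the same individual within the model". A named list of secondary outcomes is to be analysed by the same kind of model. Training group and trainer do not appear.

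**Sample size.** The Sample size calculations section derives a minimum of 57 from a repeated-measures MANOVA (effect size 0.54, power 0.95, alpha 5%). It raises this to at least 90 and says that this covers 37% attrition. It mentions no ICC or design effect.

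**The concern.** Members of one training group share peers, two trainers and 16 sessions. Anything that makes a group go well or badly moves its members' results together. Each group belongs entirely to one arm, so variation between groups passes straight into the error of the arm contrast.

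The participant intercept captures correlation between repeated measurements on one adolescent, not between adolescents in the same group. A fixed centre effect removes differences between centres, but not differences between groups within a centre.

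The protocol itself gives reason to expect some correlation. The Background credits the group format with live practice and positive peer contact, Table 1 lists group cohesion among the session objectives, and peer exposure is the stated reason for an active control. The planned model nonetheless assumes that the within-group correlation is exactly zero. If it is positive, the primary p-value and confidence interval are anti-conservative, and nothing in the model output would reveal this.

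**Working it through.** **1. The protocol's own figure.** For the MANOVA within-between interaction with 2 arms and 3 times, df1 = 2, df2 = N − 3 and λ = N·f². With f = 0.54 and N = 57, λ = 57 × 0.2916 = 16.62 and power is 0.953, so 57 is reproduced. For attrition, 57/(1 − 0.37) = 90.5, in line with the stated 90. The calculation treats participants as independent.

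**2. Number of groups.** At 1:1 allocation there are 45 per arm. 45/8 = 5.6 and 45/6 = 7.5, so 6 or 7 groups per arm and 12–14 in all.

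**3. Design effect and type I error.** The ICC is assumed, because the documents give none.
- DEFF = 1 + (m − 1) × ICC, where m is the number analysed per group.
- Actual type I error of a nominal two-sided 5% test = 2 × [1 − Φ(1.96/√DEFF)].
- Effective N at full retention = 90/DEFF.
- With 37% attrition, m = 7 × 0.63 ≈ 4.4.

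| ICC | DEFF, m = 7 | Planned SE / true SE | Type I error | Effective N of 90 | DEFF, m = 4.4 | Type I error |
|---|---|---|---|---|---|---|
| 0 | 1.00 | 1.00 | 5.0% | 90 | 1.00 | 5.0% |
| 0.01 | 1.06 | 0.97 | 5.7% | 85 | 1.034 | 5.4% |
| 0.05 | 1.30 | 0.88 | 8.6% | 69 | 1.17 | 7.0% |
| 0.10 | 1.60 | 0.79 | 12.1% | 56 | 1.34 | 9.0% |

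Across group sizes 6–8 at full retention, the type I error is 5.6–5.8%, 8.0–9.2% and 11.0–13.3% at ICC 0.01, 0.05 and 0.10.

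**4. Does fixed centre help?** Simulation under the null used 90 participants, 12 groups of 7–8, four centres as fixed effects and two post-baseline measurements, with 8,000 runs per ICC.

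| ICC | Follow-up only, group ignored | Mean of both measurements, group ignored |
|---|---|---|
| 0 | 4.4% | 4.7% |
| 0.01 | 6.1% | 6.0% |
| 0.05 | 8.8% | 9.9% |
| 0.10 | 12.8% | 14.8% |

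Mixed models fitted with a participant intercept only (300 runs each) rejected 5.7%, 9.7% and 14.7% at ICC 0, 0.05 and 0.10. The inflation therefore survives with centre in the model. A t-test on the 12 group means stayed at 4.5–5.2% for every ICC from 0 to 0.20.

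**5. Sample size on the protocol's own method.** At m = 7, 57 × 1.30 = 74.1, so 75 are needed at ICC 0.05; 57 × 1.60 = 91.2, so 92 at ICC 0.10. Both are before attrition.

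**6. Which random effect works.** Baseline precedes randomization, so training groups cannot affect baseline scores. A group intercept that is constant over time therefore largely cancels from an arm-by-time contrast that includes baseline. In a simulation with 12 groups, ICC 0.10 after baseline only and 1,400 runs, random intercepts for group and participant still gave 13% rejections for the follow-up interaction (8% with a 10-df critical value). With baseline rows excluded, the same approach gave 3.9% with 10 df.

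**The case against.** **The inflation is conditional.** A reader might infer that the type I error of this trial simply is above 5%. The documents do not support that. At ICC 0 the planned model is valid, and at 0.01 the excess is under one point. The primary outcome consists of individually set goals scaled to each adolescent's own starting level, so a sizeable ICC cannot be presumed. This stands, and it is why the result is given as a range that includes the low end.

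**Attrition reduces it.** The figures at 7 per group assume full retention. The 37% allowance shrinks the groups and lowers the error to about 7.0% and 9.0% at ICC 0.05 and 0.10. This also stands, although the protocol calls that rate larger than expected.

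**Other readings go too far.**
- The protocol does not declare peer interaction an active ingredient. It says that the source of benefit is unknown.
- Trainers are shared within a group; whether they lead several groups is not stated.
- The Statistical analyses section names only some secondary outcomes for this model, so the point does not reach every secondary outcome.
- Turning the design effect into a power loss by treating 0.54 as a standardised mean difference at one time point would mix in a separate question. The protocol's 57 is reproduced with 0.54 entered as f in the MANOVA.

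**Could it be left to an analysis plan?** That defence is weak. The article does not leave the random structure open; it names the single random effect and gives the reason for it.

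**Conclusion.** The point holds in conditional form. The protocol fixes a model that ignores training group although both arms are delivered in groups, and neither a fixed centre effect nor the participant intercept repairs this. Given a positive within-group ICC after baseline, standard errors are too small: at 7 per group they are about 0.88 of their true size at ICC 0.05 and 0.79 at 0.10. Type I error is then about 8.6% and 12.1% at full retention, or 7.0% and 9.0% at the attrition ceiling; at ICC 0.01 it is 5.7% or 5.4%.

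These figures rest on assumed ICCs, roughly equal group sizes and the design-effect formula, which the follow-up-only simulation supports. The structural omission is certain; its size is not known from the documents. The sample size shares the omission: at full retention, 90 participants are worth about 69 or 56 independent ones at ICC 0.05 or 0.10.

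**What to change.** - **Primary model, and the secondary outcomes analysed in the same way:** add a training-group random effect that acts on post-baseline measurements. Either model post-baseline scores with baseline as a covariate and a random group intercept, or, if baseline rows stay in, include a random group-by-time term. A plain group intercept alongside baseline rows is not enough (working, step 6). Use Satterthwaite or Kenward-Roger type degrees of freedom, since only about 12–14 groups are expected.
- **Data:** record training-group membership for every participant in both arms. The protocol describes attendance sheets only in the KONTAKT paragraph and for compliance, so they should not be assumed to supply it.
- **Cost analysis:** make the bootstrap inference account for training group with a method suited to few clusters. Simply resampling 6–7 whole groups per arm tends to understate the variance.
- **Sample size:** state the design effect over a range of ICCs beside the 57 and the 90.

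The cost is analysis wording and one extra recorded variable. The downside is somewhat wider intervals and fewer degrees of freedom, even if the ICC turns out to be negligible.

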### The interventions

In evaluating the feasibility and acceptability of KONTAKT© in an Australian context, a pilot version of the 16-session KONTAKT© was delivered to 16 adolescents meeting the inclusion criteria across 16 sessions in 20 weeks, with two 8-week session blocks interspersed with the Australian school holidays. After completing the KONTAKT© intervention, focus groups were held with participants, parents and trainers, capturing their perspectives of the programme. Following analysis of focus group data, final adjustments and modifications were made to the KONTAKT© 16-week variant, standardising the intervention in preparation for RCT evaluation. Tables 1 and 2 detail the structure and content of KONTAKT© (the opportunity to choose social themes/activities that reflect the participants’ personal goals or interests) and Super Chef (personal tastes for each recipe) sessions, and their emphasis on individualized activities aiming to promote motivation in the participants and generalization of skills [32].

**Table 1 Tab1:** The structure, objectives and individualized parts of weekly KONTAKT© sessions [57]

Rounds	Objective	Individualized activity
Opening	Warm-up activity, initiating conversation, promoting interaction between group members, promoting eye contact	
Reviewing homework	Reinforcing and providing feedback, troubleshooting if necessary	Sessions 2–15
Group discussion	Exchanging experiences, promoting social cognition and social relationship	Sessions 12–15
Group activities	Providing practical solutions and strategies for everyday challenging social situations, fostering a feeling of group cohesion, practicing cooperation, practising recognising and interpreting non-verbal signals, eye contact, and facial expressions	Sessions 12–15
Snack time	Practising small-talk and turn-taking in unstructured conversations	
Assigning new homework	Generalizing learnt skills to everyday social situations	Fixed: sessions 1–10 Flexible: sessions 11–14
Closing	Evaluating the session, promoting interaction between group members

**Table 2 Tab2:** The structure, objectives and individualized activities of weekly Super Chef sessions

Rounds	Objective	Individualized activity
Transition	Self-regulation and arrival into the session	
Activity 1	Sharing cooking experiences	
Activity 2	Preparation for cooking and food exploration	Every session
Snack time	Practicing small-talk and turn-taking in unstructured conversation, participating in games and activities	

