### Data collection

The data for this study will be collected by the measures as outlined in Table 3, at three time points, by an assessor blind to group allocation (1): before the intervention period (pre-intervention) (2); following the completion of the 16-week intervention (post-intervention); and (3), at 12 weeks following the intervention (follow up), with follow up being the primary endpoint. Additionally, there will be an 8-week data collection point for the cost analysis study (mid-intervention) (Table 3).

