The Experience Sampling Method (ESM) will evaluate adolescents’ everyday quality of life via daily responses from both adolescent and parent proxy report [83–85]. This 5-item measure, specifically designed for the purposes of this study, asks “In the last 24 hours, on a scale of 1 to 10 I have been feeling … ” with answers rated on a 10-point scale in five dichotomised emotional sets (sad/happy, lonely/unlonely, angry/calm, scared/unafraid, and anxious/confident). Questions are texted via mobile phones to adolescents and parents once daily from commencement of the groups to the final follow-up time point. The feasibility of this approach was assessed during a pilot study, with this method previously showing consistency across experiences and in examining the effect of social context on the daily experiences of adolescents with ASD [86].

The Treatment Satisfaction Scale (TSS-2) [87] is a short, 6-item parents’ and adolescents’ self-report instrument, measuring satisfaction with group attendance. Each item is scored on a 4-point Likert scale with response options ranging from “yes, very much” to “no”, with an open comment section, encouraging participants to freely share their experiences with the intervention.

Blind expert rating of social functioning will be assessed by an occupational therapist or psychologist, experienced in working with adolescents with ASD, and blinded to the study hypothesis, via a rating scale designed specifically for the purposes of this study. The scale requires a rating of participant’s social communication and interaction on a scale of 0–10 as observed during three video recordings of the snack times of sessions 2, 10, and 15 in both the intervention group and control groups presented in random order.

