### Outcome measures

To date, the majority of studies evaluating the efficacy of SSGT interventions in adolescents with ASD have employed the SRS-2 as the primary efficacy outcome measure, commonly scored via parent proxy report (SRS-2) [9, 17, 24, 35]. Consequently, the value adolescents with ASD themselves place on SSGT interventions and to what extent these interventions enable them to achieve personally meaningful social goals is unclear. To address this gap, the current RCT will support adolescents to set personalised goals, evaluating the efficacy of KONTAKT© through employing GAS as the primary outcome.

Previous research evaluating the quality of life of adolescents in response to SSGT has exclusively evaluated quality of life at assessment time points, most frequently at baseline, post-test and follow up, with the daily or ‘real-time’ feelings of adolescents during and after the intervention period remaining unknown [90]. To support a better understanding of the everyday feelings of adolescents during the intervention and follow-up periods, this RCT will measure participants’ daily emotions on five dichotomised emotional states (chosen by the researchers for the purposes of this study) via self and parent proxy report using experience sampling methods. This data will enable investigation of the short-term and long-term emotional trajectories of participants. There is increasing interest in whether an intervention is capable of eliciting change in biomarkers associated with ASD, one of which is eye gaze. Previous research suggests that people with ASD focus more on the mouth than eyes during emotion recognition, negatively impacting their accuracy [91]. This study will investigate for the first time the impact of the KONTAKT© SSGT programme on adolescent’s eye-gaze behaviour when viewing facially expressed emotions and their knowledge of basic and complex emotions.

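### The only model given for secondary outcomes has a participant random effect alone; if it is applied to the daily experience-sampling series, the standard errors of the trajectory terms will probably be too small

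*Protocol article*

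**What the plan says.** Statistical analyses describes a random effects regression for the primary outcome, Goal Attainment Scaling (GAS). The fixed effects are time, group, age, IQ, gender, centre and comorbidity. The one random effect is the participant's ID, "thus accounting for the correlation between measurements made on the same individual within the model". No random slope, serial-correlation structure or group-by-time term is listed. The next paragraph says that the analysis of secondary outcomes "will be conducted in a similar manner (random effects regression model"), and quality of life is in the bracketed list of those outcomes.

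The ESM is described under Secondary outcome measures as a five-item daily rating of the adolescent's day-to-day quality of life, reported by adolescent and parent. On its timing: "Questions are texted via mobile phones to adolescents and parents once daily from commencement of the groups to the final follow-up time point". The Discussion (Outcome measures) gives its purpose: "This data will enable investigation of the short-term and long-term emotional trajectories of participants".

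The cost data have their own analysis section. No separate analysis is described for the ESM.

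**The concern.** A model whose only random effect is a participant intercept implies one constant correlation between any two readings from the same adolescent, whether one day or six months apart. Once the person's mean is removed, days are treated as independent. Daily mood ratings can be expected to carry over from one day to the next, and adolescents can be expected to drift at different rates. The intercept absorbs neither. The statement that participant ID accounts for within-person correlation is tolerable for a few visits but doubtful for a series of about 200 days.

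The affected coefficients are those the ESM exists to inform: the change over days and, if a term for it is added, the arm difference in that change. Standard errors that are too small would make trends look established when they are not, across five items and two reporters. This is separate from clustering by training group. It arises within one person's series and would remain after a training-group effect was added.

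**Working it through.** **Plan's own figure.** The article states no figure for the ESM analysis. Its only related number is the recruitment target in Sample size calculations: 90 at 1:1, so 45 per arm. The stated minimum of 57 reproduces (noncentral F for the within-between interaction, 0.54 entered as f(V), 2 groups, 3 time points: power 0.9497 at 56 and 0.9533 at 57). It has no bearing on this point.

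**Length of the series.**
- Intervention: 16 weeks (Data collection: "following the completion of the 16-week intervention (post-intervention"), or 20 weeks on the pilot's calendar with school holidays (The interventions: "across 16 sessions in 20 weeks").
- Follow-up: 12 weeks (Data collection: "at 12 weeks following the intervention (follow up").
- Texts: "once daily from commencement of the groups to the final follow-up time point".
- Days: (16 + 12) × 7 = 196, or (20 + 12) × 7 = 224.
- Rows per item and reporter if every text is answered: 90 × 196 = 17,640 to 90 × 224 = 20,160.

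**Assumptions (not in the documents).** ρ is the day-to-day residual autocorrelation. s is the between-person SD of change over the whole period, in units of the within-person daily SD.

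**Formula.** Scale time from 0 to 1 and let S be the sum of squared deviations of time, S = T(T+1)/[12(T−1)]. At T = 196, S = 196 × 197/(12 × 195) = 16.50, so 1/S = 0.0606. For complete data the intercept-only model estimates the slope from within-person deviations.
- Model variance per person ≈ (1/S) × [1 + s²S/(T−1)].
- True variance per person ≈ (1/S) × (1+ρ)/(1−ρ) + s².
- The SE ratio is the square root of true over model variance, and the false-positive rate is 2 × [1 − Φ(1.96/ratio)].

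The number of participants cancels, so the ratio is the same for the day coefficient and for a group-by-day term.

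**Numbers at T = 196.**
- ρ = 0.3, s = 0: √(1.3/0.7) = 1.36; 1.96/1.36 = 1.44; about 15%.
- ρ = 0, s = 0.25: true 0.0606 + 0.0625 = 0.1231; model 0.0606 × 1.005 = 0.0609; √2.02 = 1.42; about 17%.
- ρ = 0.3, s = 0.5: true 0.0606 × 1.857 + 0.25 = 0.3625; model 0.0606 × 1.021 = 0.0619; √5.86 = 2.42; about 42%.

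The table uses the exact covariance matrix, which agrees with these approximations.

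| ρ | s | SE ratio, 196 days | False positives | SE ratio, 224 days | SE ratio, 3 visits |
|---|---|---|---|---|---|
| 0 | 0 | 1.00 | 5% | 1.00 | 1.00 |
| 0.3 | 0 | 1.36 | 15% | 1.36 | 1.09 |
| 0 | 0.25 | 1.42 | 17% | 1.47 | 1.01 |
| 0.3 | 0.25 | 1.69 | 25% | 1.74 | 1.09 |
| 0.3 | 0.5 | 2.42 | 42% | 2.54 | 1.12 |
| 0.5 | 0 | 1.72 | 26% | 1.72 | 1.13 |

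Over the wider grid (ρ to 0.5, s to 1.0) the ratio runs from 1.00 to 4.25 at 196 days and to 4.50 at 224. For three visits it reaches only 1.22 (11% false positives).

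**Check by simulation, complete data.** 1,500 null trials per scenario, 45 per arm, 196 days. For the arm difference in trend, false positives were 14% (ρ = 0.3, s = 0), 17% (0, 0.25) and 44% (0.3, 0.5). The day main effect gave 15%, 18% and 43%. The group main effect stayed near 5%. Per-person slopes compared by t-test gave 4% to 6% in every scenario.

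**Check by simulation, 30% of texts missing.** Mixed model with group-by-time term, 150 runs per setting. At ρ = 0.3 with s = 0, 0.25 and 0.5, the ratios were 1.30, 1.48 and 2.07, with false positives of 13%, 21% and 37%. Monte Carlo error is about 3 to 4 percentage points. Thinning the series weakens the effect somewhat but does not remove it. The average group difference had ratios of 0.97 to 1.11 and false positives of 3% to 7%.

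**Random slope alone.** At ρ = 0.3, s = 0.5, adding a random slope cut the ratio from 2.07 to about 1.2 (60 runs only, so imprecise). Serial correlation therefore needs its own term.

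**The case against.** The strongest objection is that the article never places the ESM under this model. The sentence about within-person correlation closes the account of the GAS analysis. The list of secondary outcomes does not name the ESM, and its quality-of-life entry could mean the PedsQL alone. The list also omits other measures from the secondary section, such as the SRS-2 and ERSSQ. This stands in part: inclusion of the ESM is a reading, not a statement. It remains the natural reading, because the ESM is presented as a quality-of-life measure within that section and no other model is offered for it.

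Secondly, the wording that extends the model to secondary outcomes fixes a class of model, not a covariance structure. A random slope with an autoregressive residual would satisfy it, and a separate analysis plan may specify one. This stands too, and makes the point conditional on the model being carried over as written.

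Thirdly, no group-by-time term is listed. Read literally, the only arm comparison is the group main effect, which is sound. That is correct. As written, the exposed coefficient is the day effect, and the arm difference in trajectory is exposed only if the interaction is added.

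A reader might infer that the ESM standard errors are bound to be far too small, or that the trial's efficacy conclusion is at risk. The documents support neither. They give no autocorrelation or drift, so the size cannot be derived from them, and the primary outcome is measured at visits.

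**Conclusion.** The point holds as a conditional one. The only model the article offers for secondary outcomes is ill-suited to a series of 196 to 224 daily readings whose stated use is trajectories. If it is applied unchanged, the standard error of the day coefficient, and of any added group-by-day term, will probably be too small.

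With autocorrelation 0.3 and drift of 0 to 0.5 within-person SD, the understatement is about 1.3- to 2.4-fold (2.5 at the top end for 224 days), with about 13% to 44% false positives at a nominal 5%. Both inputs are assumptions. Over the settings examined, the understatement vanishes only with no carry-over and identical trends for all adolescents, which is implausible for daily mood.

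The average group difference is essentially unaffected and the three-visit outcomes only mildly so. The primary GAS result is not at issue. This is a worthwhile correction to one secondary analysis, not a threat to the trial's main conclusion.

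**What to change.** In Statistical analyses, add a sentence giving the daily ESM its own model: participant random intercept, random slope for day and first-order autoregressive residual, with a group-by-day term if the arms are to be compared on trajectory. SPSS MIXED can fit this. Alternatively, reduce each participant's series to a slope, or to means for the intervention and follow-up periods, and compare the arms on those. Limit the statement that participant ID accounts for within-person correlation to the visit-based outcomes. If a separate plan already specifies an ESM model, a sentence saying so settles the point.

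The cost is wording and slightly more modelling, with no extra data, visits or participants. Intervals for ESM trends will be wider, and the fuller model may not converge for some items. The per-participant summaries are the fallback and should be named in advance.
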